## Abstract

**Background:**

Individuals diagnosed with serious mental illnesses are at increased risk of obesity- and cardiovascular-related morbidity and early mortality. Lifestyle interventions aimed at weight loss, even those adapted to suit the needs of this particular subgroup, have rarely produced clinically meaningful reductions in weight.

**Methods/design:**

The STRIDE study is a multi-site, parallel, two-arm randomized controlled translational trial. Participants were recruited from community mental health clinics and an integrated not-for-profit health system. Participants were randomized either to usual care or to a 12-month intervention that consisted of: 1) weekly group participation for six months covering topics on nutrition, physical activity and lifestyle changes; 2) monthly group participation for an additional six month maintenance period; and 3) individual monthly contacts from intervention group facilitators during the second six month phase. All participants are assessed at baseline, 6, 12, and 24 months post-enrollment. Process and implementation evaluations are included and the study design includes a cost-utility analysis. Participants include 200 individuals with serious mental illness with an average age of 47.1 years, a mean body-mass index of 38.3 kg/m^2^ and taking an average of 3.2 psychiatric medications at baseline. Baseline physiological measures included mean blood pressure (SBP/DBP) measurements of 119.2 (SD = 14.7)/79.4 (SD = 10.1); 35% reported a hypertension diagnosis and 11% took antihypertensive medications. Average lipid levels (mg/dL) were: a) triglycerides 188.0 (SD = 138.6), ranged from 43 to 1145; b) LDL 101.4 (SD = 32.9) and ranged from 17 to 185; c) HDL 45.8 (SD = 12.7) and ranged from 22 to 89; and d) total cholesterol 181.6 (SD = 39.7) and ranged from 50 to 324. Average fasting glucose levels were 108.9 (SD = 32.5) and ranged from 24 to 289. Average fasting insulin levels were 13.0 (SD=11.9) and ranged from 2 to 99.

**Discussion:**

The STRIDE study is based on a modified version of the PREMIER comprehensive lifestyle intervention, DASH diet arm. STRIDE has successfully enrolled 200 individuals with serious mental illness in community-based settings. Baseline characteristics present a population at high risk for obesity-related negative health outcomes and demonstrate the need for evidence-based interventions to reduce these risks.

**Trial registration:**

Clinical Trials.gov NCT00790517

## Background

Individuals with serious mental illnesses are at greatly increased risk of a number of medical comorbidities including obesity [1], metabolic syndrome [2-4], diabetes mellitus [4-6], and subsequent early mortality [7-9], primarily from cardiovascular disease [2,10,11]. The causes of these elevated cardiometabolic risks can include factors such as poor access to medical care [12,13], poor nutrition [14], sedentary lifestyle [11], and smoking [11,15] but they can also be exacerbated by the antipsychotic agents prescribed to treat mental health conditions [16-23]. Because many individuals diagnosed with serious mental illnesses rely on antipsychotic medications as a primary component of their treatment, complementary treatments that reduce weight gain and potentially reduce associated cardiometabolic risks have been suggested by clinicians and researchers [1]. Such treatments appear feasible [24,25] and valued by potential recipients [25] but their effectiveness has been inconsistent and, when effective, weight losses have been modest [26]. Bartels and Desilets found that manualized lifestyle health promotion programs lasting more than 3 months—combining activities with education, emphasizing weight management through improved nutrition and physical exercise—promote success but nevertheless only result in clinically significant weight loss for a minority of individuals [26]. Community-based approaches which improve the magnitude of weight loss and physical fitness are needed as well as interventions that reduce cardiometabolic risks, e.g., blood pressure, insulin resistance, or lipid levels.

This protocol describes a randomized controlled trial assessing the effectiveness of translating a known efficacious and comprehensive lifestyle intervention, adapted for individuals with serious mental illnesses at high risk for obesity, diabetes, and cardiovascular disease, and receiving community-based treatment, including antipsychotic medications, for their mental health disorders.

## Methods/design

The STRIDE study is a parallel-arm, multi-site, randomized controlled trial, translating the PREMIER comprehensive lifestyle intervention [27-30] DASH diet arm [31] for individuals taking antipsychotic medications. The primary aims are to test the hypotheses that the intervention is more effective than usual care in: 1) reducing weight and body mass index (BMI); 2) reducing fasting insulin levels and increasing insulin sensitivity; and 3) reducing total cholesterol and LDL cholesterol at 6, 12, and 24 months. Secondary aims are to explore the effects of exercise motivation, dietary motivation, social support and weight loss expectations on primary outcomes, and to examine the moderating effects of ethnicity, gender, mental health diagnostic group, medication type, and metabolic syndrome. Process and implementation evaluations are designed to identify facilitators and barriers of behavior change among participants; a cost-utility analysis will provide economic information for program planners considering adoption.

### Settings

To increase clinical relevance and the likelihood of future adoption, implementation, and sustainability of the intervention, we limited our exclusion criteria and worked with community partners to deliver the intervention in routine care settings. Our partners include two community mental health centers—Cascadia Behavioral Healthcare (Cascadia) and LifeWorks Northwest (LifeWorks)—and Kaiser Permanente Northwest (KPNW), a not-for-profit integrated health system. Cascadia serves approximately 12,000 low-income clients by providing outpatient mental health care and addiction treatment services across three Oregon counties. LifeWorks serves the mental health and addiction treatment needs of approximately 16,000 clients annually in 22 clinics throughout the greater Portland, Oregon metropolitan area. The majority of these clients come from impoverished and underserved segments of the population. KPNW provides comprehensive medical, mental health and addiction treatment to an insured population of about 480,000 members in northwest Oregon and southwest Washington. All study procedures were reviewed, approved, and are monitored by the Kaiser Permanente Northwest Institutional Review Board (other participating sites ceded authority to KPNW). All participants were informed of their rights and responsibilities as research participants and provided written informed consent prior to enrollment.

### Participants

Our sample includes individuals age ≥18 who were taking antipsychotic agents at study enrollment and who were overweight or obese (defined as BMI ≥ 27). We asked prescribing clinicians to review records for potential participants to ensure that they did not have medical or psychiatric conditions that precluded participation in a lifestyle and weight loss program that included changes to dietary practices and promotion of moderate exercise. We excluded individuals with cognitive impairment sufficient to interfere with their ability to provide informed consent, complete study questionnaires, or participate in a group intervention. We excluded women who were pregnant, breastfeeding, or planning a pregnancy during the study because reduced calorie intake may be contraindicated. We also excluded people with a bariatric surgery history or a wasting illness (e.g., cancer) because they are at increased risk for weight loss as a result of their medical status. Finally, we excluded individuals currently enrolled in another weight reduction program as inclusion could confound the results of our intervention.

### Recruitment, screening, and randomization

Using administrative and clinical databases at two sites (KPNW, Cascadia) and mental health clinician referral at the third site (LifeWorks), we identified potential study participants on the basis of their medication use, diagnoses, and current BMI. A personalized study invitation letter was prepared for each potential participant and sent to their primary care provider, psychiatrist, or psychiatric nurse practitioner, to review for suitability for the study and to co-sign if appropriate. Clinicians returned letters to study staff for mailing to potential participants. The letters provided details about the study, a toll-free study phone number, and a prepaid postcard to indicate interest in participating or to decline further contact. Letters were followed with phone calls by study recruitment staff who provided additional study details, answered questions, and conducted a brief screening. Those who met preliminary qualifications for the study were scheduled for the first screening visit.

At the first screening visit, potential participants attended a group orientation session where they received an overview of the study and had a chance to ask questions. Those who remained interested consented to having their height and weight measured. BMI was then calculated, inclusion and exclusion criteria reviewed, and eligibility established. Eligible participants completed a questionnaire and scheduled a second screening and randomization visit at which a baseline fasting blood specimen was drawn.

At the second screening visit, participants arrived having fasted for at least eight hours, had their blood drawn and their blood pressure and waist circumference measured. Individuals who had not been fasting were rescheduled. All individuals received reminder post-cards prior to the visit that included fasting and medication instructions (i.e., directions to postpone taking diabetes medications until after the fasting blood draw) and asking them to wear loose clothing to aid measurements. Participants also received reminder telephone calls the day before the visit. Following the blood draw, participants were provided with a snack and asked to take any medications at that time if they could not do so prior to the blood draw. They were then randomized to either intervention or usual care groups using a blocked, stratified procedure to ensure that group assignments remained balanced across gender and baseline BMI (27–34.9 and ≥ 35) within each site. Clinic staff involved in collecting data were blinded to participant assignment. Once group assignment was determined, non-clinic staff informed the participant and provided appropriate information about upcoming study activities. Intervention participants were notified when the group intervention was expected to begin; usual care participants were scheduled for the first follow up assessment, e.g. after 6 months. Usual care participants had no other obligation to the study and were free to initiate any weight loss effort on their own. We assessed all self-reported weight loss efforts at each follow-up for both the intervention and usual care participants.

### Tailored lifestyle intervention

The STRIDE intervention was based on the NHLBI-funded PREMIER lifestyle intervention, DASH diet arm [30]. It was designed to promote weight loss and reduce obesity-related risks, including diabetes risk, through dietary changes, moderate calorie reduction, and increased energy expenditure. Intervention targets were based on clinical practice guidelines established for obesity treatment for individuals at increased risk for cardiovascular disease [32,33]. The intervention built upon prior research [27], behavior change theories [34,35], and motivational theory [36-39] to enhance self-efficacy and promote long-term behavior change. Adaptations to content and implementation made specifically to suit this population have been described elsewhere [25]. The STRIDE intervention manual is available for download [40].

STRIDE began with a 6-month intensive group counseling phase followed by a less-intensive 6-month maintenance phase that included both group and individual contacts. Throughout both phases, implementation strategies included: frequent contacts, participant-centered group and individual facilitation approaches, and individual contacts that tailored the intervention to the participant’s preferences (as components of group meetings and separately, when needed). The program also targeted participants’ readiness to change, and encouraged group interactions that facilitated problem solving and social support, provided support for appropriate goal setting, and facilitated the acquisition of new information and skills for behavior change. Group leaders presented examples of behavioral options and used decisional balance approaches [41] to assist participants in moving toward action and setting new behavioral goals, paying careful attention to the cultural appropriateness of the program for minority participants. Sessions were designed to actively engage participants in small-group activities that fostered program ownership and allowed individual interaction with other participants and facilitators. Groups were co-led by two facilitators with complementary backgrounds; one with training as a mental health counselor, the other with training in nutritional interventions, though not a registered dietician. Having two interventionists provided flexibility during group sessions, however, and their differing backgrounds provided knowledge for managing a full range of problems and questions. All interventionists attended an initial two-day training meeting on the general intervention approach, and an additional two-day training meeting in the use of motivational interviewing techniques. In Year 1, an additional one-day training (webcast) addressed methods for presenting materials to individuals with mental illness, including those with cognitive and literacy limitations. Follow-up one-day trainings were held for all interventionists every six months. Trainers also provided ongoing supervision and individual training of all interventionists.

#### Intensive intervention (Phase 1)

The core of the intervention program was a series of weekly group meetings designed to achieve a weight loss of 4.5-6.8 kg (10–15 pounds) over a 6 month period. Groups were two hours in length and included 20 minutes of physical activity (walking). Participants received a STRIDE workbook with details on program content, self-assessments and goal-setting procedures, booklets for self-monitoring of food and activity, cooking and meal planning guides with recipes, a copy of the Calorie King book [42] to help them learn about the calorie content of typical foods, and a resistance band for strength training. Ancillary materials can be downloaded at the study website [43].

Using a manualized protocol, facilitators promoted the following specific strategies for achieving changes in behavior, activity level, and weight: 1) self-monitoring of diet and physical activity, 2) developing personalized diet and physical activity plans, 3) moderately reducing calories, 4) reducing portion sizes, substituting alternative foods, and modifying meals so that they are lower in calories and fat, 5) focusing on fruits and vegetables and increasing low-fat dairy products and fiber intake (DASH diet [44]), 6) increasing physical activity, 7) identifying situations that trigger poor diet or physical activity choices, and developing and rehearsing specific plans of action to deal with those situations, and 8) graphing behavioral progress and individual weight change.

Participants were encouraged to routinely monitor food intake, calories, and physical activity; to set reasonable short-term goals; formulate specific plans of action to achieve those goals; and to develop reinforcement and social support for carrying out each major element of the plan. Participants were also asked to keep records of servings of fruits and vegetables, servings of low-fat dairy products, and sodium and fat intake. These records were used by participants and interventionists to assess progress. Because this program placed a strong emphasis on increasing moderate-intensity physical activity, interventionists also helped participants determine how best to fit physical activity into their daily lives, taking into account each participant’s initial motivation, current activity patterns, and weekly progress. The goal was to get each participant to engage in 180 minutes per week, or about 25 minutes per day, of moderate physical activity—primarily walking. Participants were asked to record minutes of physical activity each day, as well as hours slept each night. Sleep hygiene was a module added to the original PREMIER intervention when modifications were made for this population. Other modifications included sessions focusing on stress management, advance planning for anticipated episodes of mental illness, empowering participants to engage in discourse with their prescribers regarding their medication and weight-related concerns, and tips on eating healthily on a restricted income.

Our experience has shown that willingness to make behavior changes shifts frequently during long-term weight loss intervention programs. Recognizing this reality, intervention techniques allowed group facilitators to help participants tailor weekly goals and action plans to their current stage of change. Although general guidelines for intervention components were provided by the interventionists (daily self-monitoring of caloric intake, five or more days per week of physical activity, etc.), participants were also encouraged to adjust their personal goals and action plans each week to their immediate situation, setting their own short-term goals each week in consultation with the group facilitator. Participants with no interest in physical activity were not forced to set an exercise goal, although those who declined to set a physical activity goal for several consecutive weeks were encouraged to schedule an individual brief session with the group facilitator who worked with them using motivational interviewing techniques [38]. The objective of this counseling session was to encourage reflection on long-term goals, increase motivation to engage in more physical activity, and address barriers to increased activity.

#### Maintenance intervention (Phase 2)

Where the focus of Phase 1 was on weight loss and acquisition of new information and behaviors, Phase 2 focused on maintaining weight loss through problem-solving and motivational enhancement. Because previous research has shown that greater frequency of contacts between participants and providers improves maintenance of weight loss [32], long-term obesity treatment was a priority for the high-risk participants in this study. At the same time, it is also important to recognize the difficulty of maintaining the type of high-intensity commitment required by Phase 1. Thus, Phase 2 consisted of one monthly group meeting to enhance group problem solving and social support, and one low-intensity individual session per month (by phone or e-mail) to support participants’ individualized goals without requiring time and travel to a group session. In these individual contacts, participants set the agenda and the facilitator and participants jointly reviewed the participants’ diet and activity efforts for the previous month, paying particular attention to barriers or difficulties.

### Assessment data collection and measurement

Intervention and usual care groups were assessed at baseline, 6, 12, and 24 months. Laboratory, physiological and anthropometric measures were obtained at each assessment and included: 1) height in meters measured to the nearest 0.1 cm (baseline only), 2) weight in kilograms measured to the nearest 0.1 kg (body mass index was calculated as the Quetelet index [kg/m^2^]), 3) waist circumference, measured over participants’ underwear using inelastic tape at the narrowest part of torso and measured in a horizontal plane without compressing the skin, and 4) blood pressure, measured while participants were seated with legs uncrossed and without talking after a 5-minute rest period, and then again after an additional 30 second rest period. Blood was drawn and all lab panels were collected after an overnight (8–12 hour) fast. Tests included: 5) fasting insulin, 6) fasting plasma glucose, 7) fasting triglycerides, and 8) fasting cholesterol (total, HDL, LDL).

We followed the National Cholesterol Education Program (NCEP) guidelines [45] and defined metabolic syndrome as: Individuals with 3 or more of the following risk factors: a) waist circumference greater than 102 centimeters in men or 88 centimeters in women; b) triglycerides plasma level of 150 mg/dL or greater; c) HDL-cholesterol plasma level less than 40 mg/dL for men or less than 50 mg/dL for women (or taking cholesterol-lowering medications); d) blood pressure of 130/85 mm Hg or greater (or taking antihypertensive medications), and/or e) fasting glucose greater than or equal to 110 mg/dL (or taking glucose lowering medications).

To assess insulin resistance, we calculated the Homeostasis Model Assessment Index for Insulin Resistance (HOMA-IR) as follows: fasting glucose [mmol/L] × fasting insulin [μU/mL]/22.5. This index correlates very highly with the gold standard hyperinsulinemic euglycemic clamp [46].

We included several self-reported measures to describe participants and assess health and functional status and medication use. These measures are shown in Table 1.

**Table 1 T1:** STRIDE measures and data collection schedule

	**BL**	**6 month**	**12 month**	**24 month**

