#### Analyses of secondary aims

We plan on examining the effects of exercise motivation, dietary motivation, social support and outcomes expectancies on weight change. We will also explore whether ethnicity, gender, mental health diagnostic group, medication type, and metabolic syndrome moderates the treatment effect on weight change. Furthermore, we will examine whether there was an effect of the intervention on patient reported outcomes including body image (Body Weight, Image and Self-Esteem Evaluation Questionnaire - B-WISE), psychiatric symptoms (Colorado Symptom Index - CSI), quality of life (Wisconsin Quality of Life Index - W-QLI), health-related self-efficacy (Patient Activation Measure - PAM), health (SF-36 general health subscale), and functional status (Behavior and Symptom Identification Scale - BASIS-24). Finally, we will evaluate whether dose, defined as the number of intervention sessions and number of telephone and email contacts, is related to change in the outcomes across time among participants who received the intervention.

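### The drug clause in the low-HDL item of the metabolic-syndrome rule is not tied to low HDL, so it can put some normal-HDL participants in the wrong group of one exploratory moderator analysis

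*Protocol article*

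**What the plan says.** The section on assessment data collection and measurement in the protocol article introduces the definition with "We followed the National Cholesterol Education Program (NCEP) guidelines [45] and defined metabolic syndrome as" and assigns the syndrome to "Individuals with 3 or more of the following risk factors". Three of the five items carry a medication alternative:

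- (c) low HDL: below 40 mg/dL in men, or "less than 50 mg/dL for women (or taking cholesterol-lowering medications"
- (d) blood pressure: "blood pressure of 130/85 mm Hg or greater (or taking antihypertensive medications"
- (e) glucose: "fasting glucose greater than or equal to 110 mg/dL (or taking glucose lowering medications"

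The waist item (a) has no such alternative, nor does item (b), "triglycerides plasma level of 150 mg/dL or greater".

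The variable is then used in the secondary analyses, which will explore whether "medication type, and metabolic syndrome moderates the treatment effect on weight change". It is one of five moderators named there and in the statement of aims.

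**The concern.** A medication alternative makes sense when treatment may hide the condition that the item is meant to detect. A normal blood pressure on an antihypertensive, or a normal glucose on a glucose-lowering drug, is such a case. Item (c) differs: the abnormality is an HDL that is too low, and the clause names drugs that lower cholesterol. The article itself treats lowering total and LDL cholesterol as a separate aim. Use of such a drug is therefore evidence of a different lipid problem, not of low HDL.

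Read literally, the clause can only add people to the syndrome group, and whom it adds depends on lipid-drug prescribing. If the added participants respond like those without the syndrome, the moderator contrast is pulled toward zero, and apparent prevalence rises.

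**Working it through.** **No figure to reproduce.** The article gives neither a prevalence of metabolic syndrome nor the proportion on cholesterol-lowering drugs. What follows is a reading of the rule and an illustration of size.

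**When the clause changes status.** With three of five items needed, a normal-HDL user of such a drug falls into one of three cases:

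- none or one of the other four items met: at most two with the clause, so not in the group either way;
- exactly two met: two without the clause, three with it, so status changes;
- three or four met: in the group either way.

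Example: a woman with waist 110 cm, triglycerides 160 mg/dL, HDL 65 mg/dL, blood pressure 118/76 and glucose 98 mg/dL, taking an LDL-lowering drug. She meets (a) and (b) by measurement, and the clause supplies the third item.

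**Formula.** Number changed = 200 × P(drug) × P(HDL not low) × P(exactly two of the other four), with drug use and items independent.

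**Inputs from Table 2.** 72% women, 28% men; HDL 45.8 (SD 12.7); waist 113.9 (SD 18.7); triglycerides 188.0 (SD 138.6).

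- Low HDL (normal distribution): women Φ((50 − 45.8)/12.7) = 0.630; men Φ((40 − 45.8)/12.7) = 0.324. Overall 0.72 × 0.630 + 0.28 × 0.324 = 0.544, so about 0.456 are not low. A women-minus-men HDL difference of 6 or 10 mg/dL gives 0.545 to 0.547.
- Waist item (normal distribution): 0.867.
- Triglyceride item (lognormal): 0.505.

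**Assumed, not in the article.** 35-45% meet each of the blood-pressure and glucose items; 10-40% take a cholesterol-lowering drug.

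**P(exactly two of the other four).** With blood pressure and glucose both at 0.35 it is 0.419; with both at 0.45 it is 0.391.

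At 10% use: 200 × 0.10 × 0.456 × 0.419 = 3.8. At 40% use: 200 × 0.40 × 0.456 × 0.419 = 15.3.

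**Second calculation.** A simulation from the same table assumed lognormal triglycerides, HDL and glucose, 20% on glucose-lowering drugs, component correlation 0 to 0.3, and drug use independent of or correlated with the components. About 59% had low HDL by measurement. Among normal-HDL drug users, 28-39% changed status.

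| Assumed drug use | Changed of 200, formula | Changed of 200, simulation |
|---|---|---|
| 10% | 3.5-3.8 | 1.4-3.2 |
| 20% | 7.1-7.6 | 3.2-6.4 |
| 30% | 10.6-11.5 | 5.4-9.8 |
| 40% | 14.2-15.3 | 7.8-13.0 |

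**Effect on the moderator contrast.** If everyone added responds like the non-syndrome group, the contrast shrinks by the added share of the labelled group, added/(measured + added). At the low end, with measured prevalence about 60%, this is 0.7/(60 + 0.7) = 1.2%. At the high end, 15.3 of 200 is 7.65%, and 7.65/(54.2 + 7.65) = 12.4%.

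**The case against.** The strongest reply is that counting treated patients as positive is a deliberate convention. It is applied to three items, stated openly and attributed to a guideline. Triglycerides have no drug clause, so (c) is the only place where a treated lipid disorder can count. The wording may also condense a drug list in the full protocol. The convention is indeed evident, and whether the clause matches the cited guideline cannot be checked here, so no departure from that guideline is claimed. But a convention of crediting treatment does not explain crediting treatment for a different abnormality.

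Four stronger readings are tempting, and the article does not support them:

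- **That the clause by itself puts drug users into the syndrome group.** It does not. By the calculations above, roughly 60-70% of normal-HDL users keep the same status.
- **That everyone whose status changes is misclassified.** Measured HDL is not the truth for a person whose low HDL has been corrected by treatment, and the clause places such a person correctly.
- **That the clause is redundant because HDL is measured at every assessment.** Blood pressure and glucose are too, so this argument would equally strike the clauses in (d) and (e).
- **That the trial's main results are biased.** Metabolic syndrome is not a primary outcome, eligibility criterion, stratification factor or stated covariate in the primary model, and the rule is the same in both arms.

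It is also fair to say that the attenuation is small beside the sampling error of a subgroup interaction in 200 people. That limits the importance of the point but does not remove the mismatch.

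**Conclusion.** The point holds as a minor one. As written, item (c) is satisfied by drugs that give no evidence of low HDL, and the resulting variable is a planned moderator. The change runs one way, into the syndrome group. Its size is unknown because lipid-drug use is not reported. About 1 to 15 of 200 is a range driven by the assumed 10-40% use and by the assumed distributions and item frequencies, and it includes an unknown number with treated low HDL who are correctly placed. The likely result is a modest dilution of one exploratory contrast, from about 1% to 12% if all those added respond like participants without the syndrome.

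**What to change.** For the moderator analysis, limit the medication clause in (c) to drugs that treat low HDL, classified by drug class from the self-reported medications in Table 1. This keeps (c) parallel with (d) and (e) and retains treated low HDL. Report the analysis also under the rule as now written and under measured HDL alone, as sensitivity checks, with the number of participants whose status differs.

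No new data are needed. The cost is some extra coding and two additional runs of one exploratory analysis. Table 1 does not say that indications were recorded, so drug class will be an imperfect guide to why a drug was taken; the two sensitivity checks show how much that matters.
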